### Recruitment process

2.3

Participants will be recruited through both online and offline channels. Recruitment notices will be posted on the hospital’s official website, and interested individuals may contact the research team via WeChat or telephone. Concurrently, trained research assistants will screen potential participants directly in hospital wards and outpatient clinics.

### Patient adherence

2.4

To ensure the completion of the trial, measures must be implemented to enhance patient compliance. First, researchers will comprehensively review the pathophysiology, diagnostic criteria, and current treatment strategies for PSS prior to trial initiation and ensure comprehensive empathetic communication with participants to establish mutual trust. Second, we will inform patients that acupuncture treatment is conducted on the basis of conventional treatment and rehabilitation training and it does not endanger their health to mitigate the participants’ concerns. Third, all acupuncturists involved in the trial will receive professional and standardized training before enrollment to ensure proficiency. Furthermore, all acupuncture treatments will be performed by a designated certified acupuncturist to guarantee that the patients have a favorable experience. Additionally, our research team will maintain regular, transparent communication with participants and their caregivers to foster a shared understanding of the patient’s clinical condition and encourage them to receive active engagement in the acupuncture treatment. Patients will be clearly informed that all trial-related examinations (such as surface electromyography (sEMG) and shear-wave ultrasound elastography), scale assessments, and 12 acupuncture treatments are free of charge. Finally, all adverse events and participant dropouts during the trial will be documented.

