## Abstract

**Background:**

Post-stroke spasticity (PSS) is a common motor complication during stroke recovery, imposing a substantial burden on both individuals and society owing to its high morbidity and disability rates. Current evidence suggests that acupuncture may be an effective intervention for alleviating PSS; however, the efficacy and safety remain uncertain owing to methodological limitations and the generally low quality of the existing evidence. Therefore, this study aims to evaluate the efficacy, feasibility, and safety of acupuncture for PSS and to explore the underlying anti-spasticity mechanisms.

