Research indicates that acupuncture ameliorates motor dysfunction by activating the primary motor cortex (M1) of the ipsilesional hemisphere and promoting brain network remodeling in motor-related areas (12). Acupuncture is currently used to treat PSS. Clinical evidence suggests that acupuncture can alleviate spasticity, enhance motor function, and accelerate rehabilitation and has received a Grade B recommendation for PSS management (13). Experimental studies indicate that acupuncture ameliorates PSS through multiple mechanisms. It modulates the Glu/GABA–glutamine (Gln) cycle via glutamate transporter 1 (GLT-1), thereby rebalancing Glu/GABA levels and mitigating spinal hyperreflexia (14). In addition, it enhances cerebral blood flow in the ischemic penumbra and restores spinal inhibitory control via 5-hydroxytryptamine receptor 2A (5-HT_2A_R)-dependent potassium–chloride cotransporter 2 (KCC2) reactivation, thereby improving limb spasticity (15). However, the majority of the studies are of low methodological quality and lack standardized acupuncture protocols and rigorous study designs. In addition, the potential placebo effects remain incompletely characterized, which may hinder definitive conclusions. Further high-quality research is essential to validate the efficacy and safety of acupuncture for PSS and to elucidate the underlying neuromuscular mechanisms, providing more reliable, evidence-based guidance for personalized prophylaxis and therapy for PSS.

As a solution, we designed a pilot randomized controlled trial (RCT) to assess the preliminary efficacy, feasibility, and safety of acupuncture for PSS and explore the underlying anti-spasticity mechanism of acupuncture.

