### Safety and adverse events

2.8

The acupoints selected in this trial are based on a consensus among acupuncture experts and are considered relatively safe. Potential adverse events included pain, numbness, subcutaneous swelling, bruising, fainting during acupuncture, needle sticking, or needle bending. If an adverse event occurs, it will be recorded in detail in the Case Report Forms (CRFs). Serious adverse events, such as syncope, deep tissue infection, or abscess, will be promptly reported to the Ethics Committee, and affected participants will be immediately withdrawn from the trial and provided with active and effective treatment.

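### Section 2.4 plans to assure participants that acupuncture poses no danger to health, which conflicts with the risks listed in section 2.8 and with the trial's aim of studying safety

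*Protocol article*

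**What the plan says.** Section 2.4 of the protocol article lists steps to improve compliance. The second is to inform patients that "acupuncture treatment is conducted on the basis of conventional treatment and rehabilitation training and it does not endanger their health", with the stated purpose of easing their concerns. The same section ends by promising that "all adverse events and participant dropouts during the trial will be documented".

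Section 2.8 (Safety and adverse events) says of the chosen acupoints that they "are considered relatively safe". It continues: "Potential adverse events included pain, numbness, subcutaneous swelling, bruising, fainting during acupuncture, needle sticking, or needle bending". On serious events it says: "Serious adverse events, such as syncope, deep tissue infection, or abscess, will be promptly reported to the Ethics Committee". Affected participants are then to be withdrawn and treated.

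The Abstract says of acupuncture for this condition that "the efficacy and safety remain uncertain". The Introduction gives the purpose of the trial as "to assess the preliminary efficacy, feasibility, and safety of acupuncture for PSS".

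**The concern.** The protocol plans to give participants, as settled fact, an answer on safety that it elsewhere treats as open. The assurance is also hard to square with the protocol's own examples of serious events, which it foresees clearly enough to set a reporting route for them.

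What is at stake statistically is the adverse-event record, the only evidence the trial will have for its safety aim. Some of the listed events reach the record mainly because a patient mentions them. If patients have been told by the research team that the procedure poses no danger, some may judge a symptom not worth mentioning. Any resulting bias would run one way, toward fewer recorded events and a more favourable apparent safety profile.

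**Working it through.** No formula or planned figure is involved, so the check sets the statements side by side.

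**1. Is there a contradiction?**

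| Place | Position on safety |
|---|---|
| Section 2.4 | No danger to health; no qualifier |
| Section 2.8, opening | Acupoints safe in a relative sense only |
| Section 2.8, potential events | Seven kinds of event named |
| Section 2.8, serious events | Three examples, with notification, withdrawal and treatment |
| Abstract, Background | Safety uncertain |
| Abstract, Introduction, Conclusion | Safety is something the trial will evaluate |

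The first row cannot stand with the others. The minor events alone might be reconciled with it, since a bruise need not be called a danger. The serious examples cannot, and neither can the statement that safety is unresolved.

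**2. Which events could the message affect?** Section 2.8 names seven potential events. Staff can observe five of them: swelling, bruising, fainting during a session, a stuck needle and a bent needle. That leaves 7 − 5 = 2, pain and numbness, which depend mainly on the patient speaking up. Section 2.6.1 adds a complication: real needling aims at deqi, described as soreness, distension and heaviness. The patient therefore has to judge which sensations are expected and which to report, and a prior assurance bears on that judgement.

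**3. What in the plan works against under-reporting?** Sections 2.4, 2.8 and 2.10 all say that adverse events will be recorded, and Table 1 schedules this in each of weeks 1 to 4. The article does not say whether symptoms are elicited by spontaneous report, open question or checklist. The recording commitments therefore cover events that staff come to know of; they do not show that the effect of the message is offset.

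**4. What would under-reporting do to the comparison?** Assume, since the documents give nothing on this, that a fraction *s* of subjective events goes unreported in both needled arms, with true rates *p*A (acupuncture) and *p*S (sham).

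- Observed rates: *p*A(1 − *s*) and *p*S(1 − *s*)
- Observed difference: (*p*A − *p*S)(1 − *s*), shrunk by the factor (1 − *s*)
- Observed ratio: *p*A/*p*S, unchanged

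Absolute rates and the difference would be understated, while the ratio would survive under this equal-fraction assumption. The documents give none of *p*A, *p*S or *s*, so no numerical size can be stated.

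**The case against.** **The sentence may only mean that acupuncture is added to standard care and does not replace it.** That is a fair reading of its first half. The second half is a separate claim about health, joined by a conjunction and left unqualified. This reading softens the conflict but does not remove it.

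**Not endangering health is different from causing no side effects, and most of the listed potential events are minor and local.** This stands for the minor events. It does not cover the serious examples in section 2.8.

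**The plan requires adverse events to be documented, and no passage discourages reporting.** This stands, and it limits the point. A reader might infer that the message demonstrably suppresses reporting, or that a low event count would be worthless. The documents support neither: no suppression is shown, and most of the listed events can be seen by staff. What remains is a plausible route for bias in pain and numbness.

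**The consent form may set out the risks in full.** It may. Section 2.2.1 requires written consent, section 2.1 reports ethics approval, and the consent pages are not available here. A reader might infer that informed consent is undermined; that cannot be concluded. But if the form does list the risks, the section 2.4 message would conflict with it as well.

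**A reader might also infer that patients would delay seeking care for a late infection.** Nothing in the documents bears on this, and it forms no part of the point.

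**Conclusion.** The contradiction is real and rests only on the article's own text. Section 2.4 plans an unqualified assurance that is inconsistent with the risks in section 2.8 and with the status of safety as an open question and study aim.

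The consequence for the data is possible, not shown. The message may reduce reporting of subjective symptoms and so make acupuncture look somewhat safer than it is. That rests on two assumptions: that participants take the assurance as guidance on what to mention, and that elicitation does not fully correct for it. Its size cannot be derived from the documents.

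The reach is limited. Section 2.7 lists adverse events as neither a primary nor a secondary outcome; they appear in section 2.8 and Table 1. Efficacy outcomes, sample size, randomization and analysis are unaffected. The change is still worth making, because it alters what participants are told and costs almost nothing.

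**What to change.** Delete the assurance from section 2.4 and reconcile that section with section 2.8. Replace it with a neutral statement, worded identically for the acupuncture and sham arms so that it gives no clue to allocation, making four points:

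- acupuncture is given in addition to conventional treatment and rehabilitation;
- the events listed in section 2.8 are possible;
- safety is one of the things being studied;
- participants should report any symptom.

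The first point keeps the legitimate reassurance about standard care. The last helps protect the completeness of the adverse-event data.

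The cost is a change to the participant briefing only. The possible downside is a slight rise in refusals or dropout.

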### Randomization, allocation concealment, and blinding

2.5

Eligible trial participants will be randomly assigned to one of three groups—acupuncture, sham acupuncture, or conventional treatment—using block randomization implemented in the Statistical Package for Social Sciences (SPSS, IBM Corp., NY, USA), version 27. Stratification will be performed according to sex, age, disease duration, and stroke subtype. Randomization codes will be generated by an independent research assistant, placed in sequentially numbered, opaque, sealed envelopes, and distributed to participants only after the completion of baseline assessments.

Participants, outcome assessors, and statisticians will remain blinded to the group allocation throughout the trial. Given the nature of acupuncture intervention, acupuncturists could not be blinded. Blinding codes were securely maintained by an independent researcher who was not involved in participant recruitment, treatment delivery, or outcome assessment. To preserve blinding integrity, participants will be assessed and treated in individual quiet rooms equipped with partition curtains to prevent communication among participants.

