**Methods:**

This study is a prospective, randomized, controlled trial. A total of 180 patients diagnosed with post-stroke spasticity (PSS) will be enrolled and randomly assigned in a 1:1:1 ratio to one of the three groups: acupuncture, sham acupuncture, or the basic treatment group. Participants in the acupuncture and sham acupuncture groups will receive a 4-week intervention, followed by a 4-week follow-up period. In contrast, the basic treatment group will receive only conventional medical management and standardized rehabilitation training without any acupuncture-related procedures. The primary outcome measure will be spasticity severity, assessed using the Modified Ashworth Scale (MAS). The secondary outcomes will include motor function (Fugl-Meyer Assessment, FMA), clinical spasticity (Clinical Spasticity Index, CSI), neurological impairment (National Institutes of Health Stroke Scale, NIHSS), activities of daily living (Modified Barthel Index, MBI), neuromuscular activity (surface electromyography, sEMG), and muscle mechanical properties (ultrasonographic elastography, UE). The FMA, CSI, NIHSS, and MBI will be evaluated at baseline, week 2, week 4 (end of treatment), and the 4-week follow-up visit. The MAS, sEMG, and UE will be assessed at baseline and at the end of the 4-week treatment period.

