#### Basic treatment group

2.6.3

Participants will not receive acupuncture treatment in this group but will only receive conventional therapy and rehabilitation training recommended by the Stroke Prevention and Treatment Guideline 2024 (SPTG 2024). Patients in this group who complete follow-up are eligible for a complimentary 4-week (12 sessions) acupuncture treatment.

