### Quality control and data management

2.10

Outcome assessors will collect all participant data using paper-based CRFs and subsequently enter the data into an electronic database. The research team will conduct periodic data monitoring to verify completeness, accuracy, and authenticity while concurrently tracking trial progress and adherence to the intervention protocol. To enhance adherence, researchers will maintain regular contact with the participants via telephone or WeChat, providing reminders to actively engage in treatment, scheduled assessments, and follow-up visits. All adverse events and reasons for participant discontinuation—whether from the trial or from follow-up—will be systematically documented.

Acupuncturists, outcome assessors, and statisticians will all receive standardized training on the study protocol to ensure a full understanding of the study procedures and details. Specifically, acupuncturists will complete comprehensive professional training covering acupoint selection and localization, acupuncture techniques, treatment frequency and duration, and distinct protocols for both verum and sham acupuncture, thereby ensuring intervention consistency and fidelity across all participants. All members of the research team will attend scheduled organizational meetings every three weeks to review the progress, identify challenges, and collaboratively resolve issues arising during the trial.

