### Limitations

3.3

This study has several limitations. First, as a single-center, exploratory, randomized controlled trial conducted primarily at one hospital in Beijing, it may not fully capture the diversity of the patient population, which may lead to selection bias. Thus, large-scale, multi-center RCTs are needed to confirm the definite efficacy of acupuncture for PSS in the future. Second, the age of participants was restricted to 35–75 years to ensure relative pathophysiological homogeneity within the study population and to minimize age-related confounding. Although this design strengthens internal validity, it limits the direct extrapolation of the findings to older patient populations. Third, given the restrictions of equipment, cost, and time, the study mainly emphasized the neuromuscular effect mechanisms of acupuncture without delving into the central regulatory mechanisms or exploring acupuncture-induced neural plasticity. Finally, given the complex nature of acupuncture intervention, blinding of the acupuncturists was not feasible, which may have introduced performance bias and affected the interpretation of the results.

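### Section 2.5 claims blinding of all participants and assessors, but basic-group patients know their arm, and the section 2.10 data-collection rule exposes the MAS assessor to arm-revealing information

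*Protocol article*

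**What the plan says.** Section 2.5 makes an unqualified claim: "Participants, outcome assessors, and statisticians will remain blinded to the group allocation throughout the trial". The one exception it names is the treating staff: "Given the nature of acupuncture intervention, acupuncturists could not be blinded". Section 3.3 repeats that exception alone ("blinding of the acupuncturists was not feasible").

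On the third arm, section 2.6.3 says "Participants will not receive acupuncture treatment in this group but will only receive conventional therapy and rehabilitation training", and the abstract says "the basic treatment group will receive only conventional medical management and standardized rehabilitation training without any acupuncture-related procedures". Sections 2.1 and 2.6.3 offer this group 12 acupuncture sessions once follow-up is complete.

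On data collection, section 2.10 says "Outcome assessors will collect all participant data using paper-based CRFs" and has the same assessors enter the data into the database. Section 2.8 places adverse events in the case report forms. Section 2.9 gives the blinding questionnaire to the acupuncture and sham groups only.

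**The concern.** There are two separate problems.

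The first is a false statement about participants. A patient who is never needled, and who is offered needling later, is not blinded. A reader of section 2.5 would take the acupuncture-versus-basic comparison to be protected from patient expectation, and it is not.

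The second is a conflict about assessors. Section 2.5 says they are blinded, while section 2.10, taken literally, has them handle information that can give the arm away. The primary outcome is the change in MAS from baseline to week 4 (section 2.7.1). Section 3.2 itself says that scale ratings depend heavily on the assessor and that subjective influence cannot be removed. Blinding the rater is the main protection for such an endpoint, and a rating made with knowledge of the arm cannot be repaired after data collection.

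**Working it through.** No figure in the plan is in dispute, so the check sets the statements side by side.

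**Participants**

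1. Claim: participants are blinded, with no arm excepted (2.5).
2. Basic arm: no acupuncture-related procedure (abstract, 2.6.3) and free sessions after follow-up (2.1, 2.6.3).
3. Patients must be fully conscious and able to take part in interviews and follow instructions (2.2.1), so they will notice that they are not needled.
4. The blinding device (retractable needle, matched pads) is described only for the sham group against real acupuncture (2.6.2), and the blinding check covers only those two groups (2.9). Nothing masks the basic arm.
5. Size: with 1:1:1 allocation, 180 / 3 = 60 participants, one third of the trial, for whom the claim fails.
6. Disclosure: section 3.3 names the acupuncturists only.

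**Assessors**

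1. Claim: assessors are blinded throughout (2.5).
2. Rule: assessors collect all participant data on the forms and enter them (2.10).
3. Adverse events are on those forms (2.8), and several of those listed can arise only from needling, such as stuck or bent needles. Recording one shows that the patient is not in the basic arm. Bruising or swelling under the skin also hints at real rather than sham needling, because the sham tip does not penetrate (2.6.2).
4. The questionnaire exists only for the two needle arms (2.9), so its presence or absence separates needled from basic patients. The patient's guess does not by itself identify real versus sham.
5. Compliance is listed in Table 1 without restriction by arm. It separates needled from basic patients only if it records needling sessions.
6. Timing: Table 1 schedules adverse events, blinding assessment and compliance in weeks 1 to 4, and the primary MAS rating falls at week 4. Adverse events from earlier weeks would therefore be known before that rating if the assessor records them as they occur.
7. No statement in the article separates the MAS rater from the person who collects these items. The individual rooms and curtains in section 2.5 stop participants talking to each other, not to the assessor.

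Steps 1 to 3 of the assessor check rest on the text. Steps 4 and 5 rest on reading the general rule in section 2.10 together with Table 1, because no sentence assigns the questionnaire or compliance record to assessors by name.

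**The case against.** The strongest reply is that the participant part is loose wording. Sections 2.9 and 3.1 show that blinding was meant for acupuncture versus sham, with the basic arm as a reference. On assessors, a condensed article commonly leaves to the full protocol who completes which form page. Section 2.8 does not say who records adverse events, section 2.9 does not say who gives the questionnaire, and section 2.5 places the codes with an independent researcher.

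Part of this stands. The intended scope can be inferred, participant blinding between acupuncture and sham is plausible as designed, and it is not shown that the questionnaire or compliance record reaches the rater before the week-4 MAS. But the sentence in section 2.5 is still wrong as written and section 3.3 does not correct it. Nor is section 2.10 silent: it states a rule, and that rule conflicts with section 2.5.

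A reader might infer three stronger points that the document does not support.

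- That acupuncture versus basic is simply open label. If assessors and statisticians are masked as section 2.5 says, the comparison is participant-unblinded but assessor-blinded.
- That the team meetings unblind assessors ("All members of the research team will attend scheduled organizational meetings every three weeks"). The text describes reviewing progress and resolving issues, and mentions no discussion of individual participants or allocation.
- That the bias can be sized against the planned acupuncture-versus-basic difference of 2.58 − 2.19 = 0.39 (section 2.11). Any bias set against it would be assumed. MAS is taken on two muscles bilaterally with no stated aggregation, so even the scale of 0.39 is unclear.

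**Conclusion.** The point holds in two parts of different strength. The participant-blinding claim is false for 60 of 180 patients, which follows directly from the text, and the limitations section omits it. The assessor-blinding claim conflicts with the data-collection rule as written. This is firm for needle-specific adverse events and is a plain-reading inference for compliance and the questionnaire. The exposure can separate needled from basic patients and hint at real versus sham needling. It does not establish that any assessor will in fact be unblinded. The size of any bias in MAS cannot be computed from the document. The plan should be corrected because the remedy is cheap and the harm cannot be undone once ratings are made.

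**What to change.** 1. In section 2.5, limit participant blinding to acupuncture versus sham. Describe comparisons with the basic arm as participant-unblinded and assessor-blinded, and add this to section 3.3 as a limitation.
2. In section 2.10, have outcome assessors complete only the outcome measures. Existing study staff who do not rate outcomes should record adverse events, session compliance and the blinding questionnaire on a separate form that assessors neither see nor enter. The person giving the questionnaire should also not be treating the patient, so that nobody who knows the allocation asks the patient to guess it.

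The label of assessor-blinded in item 1 is only as good as item 2. The cost is a wording change, a reallocation of form pages among existing staff and slightly more form handling. Sample size, outcomes and visits are unaffected.
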